### Data management

The data for this multi-site surveillance will be centrally managed in a cloud based infrastructure that is appropriately secured to ensure participant confidentiality and compliance with local laws. In the community data will be gathered on android tablets using android application package *‘EntericFev’* developed in house and stored in PostgreSQL databases on an Amazon cloud EC2 instance. Clinic and laboratories will use a secured web browser based application to upload and edit data. A comprehensive audit trail enabled database management solution for data managers and a real-time dashboard for the project managers permit careful monitoring and implementation of the surveillance.

### Data analysis

Incidence rates will be calculated as the number of discrete events of illness (for confirmed typhoid fever and acute febrile illness) over the total person-time under observation and at risk. Recurrent events will be allowed to include multiple episodes of illness over the study period. The person-time for each child will begin from the date of enrolment to the end of follow-up or date of loss to follow-up. Time with illness and when children not under surveillance will be excluded from the calculation of person-time. Rates will be expressed as per 1000 child-years. The two-year study period will be divided into three age intervals (6 m – 4 years, 5-9 year and 10-14 years) determined by the chronological age. The incidence rates for each age interval will be calculated based on the number of children at risk in the beginning of each interval, the number who had the event and the number who were lost to follow-up. The age-specific rates will be calculated as the number of new cases of illness in the specific age interval divided by total number of person-years of follow-up contributed by all children at risk in this interval. Children will be allowed to move higher up in the age intervals. Because recurrent events of illness will be considered, we will account for correlation at the level of individual child using mixed effects poisson regression model. All statistical analysis will be performed using Stata 14.0 (Stata Corp).

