## Background

Salmonella Typhi is the leading cause of enteric fever cases responsible for between 12 and 21 million illness episodes and over 140,000 deaths each year globally [1, 2]. The disease is largely prevalent in the low and middle income countries of South Asia. Three community-based cohort studies conducted between 1995 and 2006 in India estimated the incidence of culture confirmed typhoid at 377 (178–801) per 100,000 person years with the highest incidence in early childhood [3–5]. The burden of enteric fever is predicted to worsen with the emergence of multi-drug resistant strain H58 in this region.

The World Health Organization (WHO) in its position paper on typhoid published in 2008 [6] recommends the use of typhoid vaccines to prevent infection in high-risk populations, particularly where antibiotic resistance is prevalent. These recommendations have remained unimplemented in India partly due to a perceived decline in the incidence and severity of typhoid fever in recent hospital-based reports accompanied with evidence of heterogeneous distribution of disease. These findings of declining disease burden in hospital based studies can partly be attributed to the indiscriminate early use of antibiotics to treat febrile illness. Newer antibiotics, that are increasingly accessible over the counter, have been shown to decrease transmission of this host-restricted organism when administered appropriately, early in disease [7–9]. Furthermore, antibiotics decrease culture confirmation by achieving defervescence in ambulatory care where cultures are generally not performed and by decreasing the sensitivity of blood culture post antibiotic therapy. In the absence of an alternative diagnostic assay of sufficient diagnostic accuracy, estimation of disease burden continues to rely on isolation of the organism by blood culture that is likely to be influenced by prior treatment and healthcare seeking behaviour.

While it is challenging to disaggregate the complex interplay between antimicrobial use, antimicrobial susceptibility and disease burden, estimating age-specific incidence of typhoid in the community by investigating febrile episodes prior to antimicrobial therapy will provide a better understanding of current disease burden and its transmission dynamics.

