## Methods

### Hypothesis

Active, community-based surveillance will estimate the true incidence of typhoid fever and provide a better understanding of transmission of typhoid in the population than available data from hospital based extrapolations.

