In the event of fever, a daily follow up will be established until there are three consecutive fever free days. A digital thermometer and a fever diary card will be provided, and primary caregivers will be trained to use the thermometer and document the temperature three times a day. The study team will also document the temperature of the child in the fever diary card during home visits. At each daily contact during the fever follow up, the study team will document information pertaining to the previous calendar day including the highest documented temperature. If the child has any serious illness the parents will be encouraged to seek healthcare from their preferred provider. The family will be informed the need to avoid antibiotics and over the counter medicines that are not prescribed by their physician.

Any reported fever for 3 or more consecutive days will be designated as ‘Suspected Typhoid Fever’ and the child will be encouraged to visit the study clinic. At the study clinic the child will be evaluated by a study physician on the fourth day of fever and if there is history of fever in the preceding 12 h a blood culture will be requested. If the child has been afebrile for over 12 h, unless clinically indicated the blood culture will be deferred. Any subsequent fever within the next 24 h will warrant a blood culture. Prior antimicrobial therapy will not be a contraindication for blood culture. If a child has received a blood culture in the previous 14 days, blood culture will be withheld unless it is requested for by the clinician treating the participant.

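### The typhoid rate is not corrected for suspected fevers that are never cultured, so it estimates a minimum culture-confirmed incidence, not the true incidence named in the hypothesis

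*Protocol article*

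**What the plan says.** The Hypothesis states: "Active, community-based surveillance will estimate the true incidence of typhoid fever". The first objective is narrower: age-specific incidence of culture-confirmed typhoid.

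The Data analysis section fixes the estimator: "Incidence rates will be calculated as the number of discrete events of illness (for confirmed typhoid fever and acute febrile illness"), taken "over the total person-time under observation and at risk". It adds: "Time with illness and when children not under surveillance will be excluded from the calculation of person-time". It mentions no adjustment for culture uptake or culture sensitivity.

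Under Study design, a reported fever of three or more consecutive days is suspected typhoid, and "the child will be encouraged to visit the study clinic". Two rules then limit culture:

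- "If the child has been afebrile for over 12 h, unless clinically indicated the blood culture will be deferred". Fever returning within the next 24 hours reopens the request.
- "If a child has received a blood culture in the previous 14 days, blood culture will be withheld", unless the treating clinician asks for it.

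Prior antimicrobials do not bar culture, although the Background says antibiotics reduce confirmation, among other ways "by decreasing the sensitivity of blood culture post antibiotic therapy". Laboratory methods keeps serology out of the estimates but counts S. Typhi from other normally sterile sites.

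**The concern.** A suspected fever without a culture contributes nothing to the numerator, while the child's well time before and after it stays in the denominator. In effect it is scored as not typhoid. The loss runs in one direction and is proportional to the share of typhoid episodes that escape culture.

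The Background and Discussion fault hospital data for missing cases through care-seeking behaviour and early antibiotic use. The crude rate here remains open to both influences, though to a lesser degree. If it came out low, it could be read as low burden when part of the shortfall is incomplete culture. The Discussion intends the results to inform whether and how vaccine is used, so that misreading would matter.

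**Working it through.** **1. The plan's own figure (Sample size section).** Child-years per site: 5600 × 1.5 = 8400, as stated. The exact two-sided 95% lower Poisson limit for x cases is χ²(0.025; 2x)/2, divided by child-years.

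- x = 26: rate 26/8.4 = 3.10/1000, interval 2.02 to 4.54.
- x = 25: lower limit 1.93/1000.

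So 26 is the smallest count that excludes 2/1000, and the plan's threshold reproduces. It refers to observed cases; reading it as a statement about underlying incidence takes every episode as cultured and detected.

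**2. Effect of coverage on the culture-confirmed rate.** Let c be the share of culture-confirmable typhoid episodes that are in fact cultured. The protocol gives no value, so c is an assumption. The observed rate is the culture-confirmable rate × c, expected cases are that rate × c × 8.4, and the chance of 26 or more cases is the Poisson upper tail. For a culture-confirmable rate of 4/1000, which lies within the plan's anticipated 1 to 5/1000:

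| c (assumed) | Observed rate /1000 | Expected cases | P(26 or more) |
|---|---|---|---|
| 1.0 | 4.0 | 33.6 | 0.92 |
| 0.9 | 3.6 | 30.2 | 0.80 |
| 0.8 | 3.2 | 26.9 | 0.59 |
| 0.7 | 2.8 | 23.5 | 0.33 |

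**3. Shortfall against true incidence.** This is a separate calculation with a different starting point. If 4/1000 is the true typhoid rate, observed = true × c × sensitivity. With assumed c of 0.7 to 0.9 and assumed sensitivity of 0.5 to 0.7:

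- low end: 4 × 0.7 × 0.5 = 1.4/1000
- high end: 4 × 0.9 × 0.7 = 2.52/1000

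The range lies on both sides of the plan's 2/1000 benchmark.

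**4. Does excluding illness time repair this?** No. Assuming 0.5 to 2 suspected episodes per child-year, each removing 7 to 14 days, the share of person-time removed runs from 0.5 × 7/365.25 = 1.0% to 2 × 14/365.25 = 7.7%. That trims the denominator slightly but does not restore a missing case.

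**The case against.** The strongest reply is that the estimator matches the objective, which claims only culture-confirmed incidence. On this view the conflict comes down to a phrase in the Hypothesis, whose full sentence contrasts the study with hospital-based extrapolation. This holds for sensitivity: missed detections conflict with the Hypothesis, not with the objective. It does not hold for coverage, because a typhoid episode that culture would have confirmed but that was never cultured is lost to the objective's own target.

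Second, this is a condensed article, and weighting or sensitivity analyses may sit in a document not shown. That is possible. But the point does not rest on an omission alone: the text states an unadjusted estimator and a claim that this estimator cannot meet.

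Third, the design limits the problem. It has weekly contact, daily fever follow-up and advice against unprescribed antibiotics. Families must be willing to have investigations, and both culture rules have exceptions. The Background also admits that culture-based burden is influenced by treatment and care seeking. All this stands and may keep the loss small, but it does not bring coverage to 100% or measure it.

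A reader might go further in three ways that the protocol does not support:

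- That the bias differs by age and site. It may, but no uptake or antibiotic figures are given by age or site. The smaller blood volume applies only to children from 6 months to 1 year, and nothing in the text says that it changes sensitivity.
- That a culture-confirmable rate of 4/1000 would shrink to 1.4 to 2.5/1000. That applies sensitivity twice, because such a rate already contains only what culture can detect. The range holds only from a true rate of 4/1000.
- That every fever meeting the 12-hour or 14-day rule goes uncultured, or that all person-time is counted. The exceptions and the exclusion of illness and unsurveilled time contradict both.

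**Conclusion.** The concern holds in this form: the stated estimator yields, in expectation, a minimum culture-confirmed incidence, and it falls further below true incidence because culture sensitivity is imperfect and is reduced by prior antibiotics. Calling it a minimum assumes that false-positive cultures are negligible and that isolation from other sterile sites recovers few uncultured cases.

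The size is unknown from the protocol. Under assumed coverage of 70% to 90%, the culture-confirmed rate is understated by 10% to 30%, and at 4/1000 the chance of reaching the 26-case threshold drops from 0.92 to between 0.33 and 0.80. These figures take coverage among typhoid episodes as the quantity that matters; it need not equal coverage among all suspected fevers. The plan should be changed, but this does not invalidate the study: the crude rate remains usable if it is labelled for what it is.

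**What to change.** In the Data analysis section:

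- Label the crude rate as minimum culture-confirmed incidence.
- Report the share of suspected typhoid fevers cultured, by site and age band.
- Beside the crude rate, give one adjusted for coverage: weight each blood-culture-confirmed case by the inverse of the estimated probability that such a fever was cultured, modelled on age, site, fever duration and prior antibiotic.
- Give a further estimate over a stated range of culture sensitivity, split by prior antibiotic.
- Treat a fever within 14 days of a culture as uncultured only if it is a new episode. Counting a continuation of an already cultured illness as uncultured would inflate the weights and bias the adjusted rate upward. The rule separating the two must be written down.

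In the Hypothesis, replace the claim of true incidence with wording that matches.

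No change to field procedures or culture rules is needed. Fever days and treatment are already recorded, and culture status should follow from the clinic and laboratory data. The price is analysis time, a wider interval for the adjusted rate, and reliance on the untestable assumption that uncultured fevers resemble cultured ones with the same covariates. That is why the crude rate should stay alongside it.

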### Sample size

The incidence of acute typhoid fever in children aged 6 months to 15 years in India was previously estimated to be between 6 and 12 per 1000 child years (CY) with the highest rates in 1–4 year olds [4, 10]. If community-level incidence has declined as hospital-based estimate suggest, the current incidence in this age-group would be between 1 and 5 per 1000 CY. Recruiting, at each site, a cohort of 5600 children between 6 months and 13 years + 364 days will provide 8400 child years of observation over 18 months that would be distributed approximately as 2400 child years in the 6-month to 4 years, and 3000 child years in the 5–10 and 11–14 age groups in an open cohort and assuming a uniform death rate. Accumulating 8400 child-years will exclude an incidence rate of 2/1000 with 95% confidence if there are 26 or more cases (IR > 3/1000) in the cohort. In turn, this sample size will be adequate to exclude at 95% confidence limits, a rate of 2/1000 in each of the 6 months-4 years, 5–10 and 11–14 years age groups in which the observed incidence is 4/1000 or greater using a Fishers exact test based on the formula (Armitage,1971; Snedecor & Cochran,1965) as described in Epidemiologic Analysis with a Programmable Calculator, 1979.

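### The child-level mixed-effects Poisson model does not, by default, give an interval for the population incidence rate that the plan defines; a marginal model would.

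*Protocol article*

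**What the plan says.** All of this is in the Data analysis section of the protocol article, unless stated otherwise.

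- Overall rates: "Incidence rates will be calculated as the number of discrete events of illness (for confirmed typhoid fever and acute febrile illness) over the total person-time".
- Age-specific rates: "The age-specific rates will be calculated as the number of new cases of illness in the specific age interval divided by total number of person-years", counting only time spent in that interval.
- Scale: "Rates will be expressed as per 1000 child-years".
- Repeats: "Recurrent events will be allowed to include multiple episodes of illness over the study period".
- Inference: for repeat episodes, the stated method is to "account for correlation at the level of individual child using mixed effects poisson regression model".
- Software: "All statistical analysis will be performed using Stata 14.0".

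The Objectives ask for age-specific incidence of culture-confirmed typhoid and for a description of the incidence of acute febrile illness. The Sample size section says that the cohort at each site "will provide 8400 child years of observation over 18 months", and that 26 or more cases would exclude a rate of 2 per 1000 with 95% confidence.

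The article does not give the distribution of the random effect, and does not say how output from the model relates to the crude rates.

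**The concern.** Events divided by person-time is a marginal quantity: the average rate over all children in the cohort. A Poisson model with a log link and a normal child-level intercept is parameterised differently. Its exponentiated intercept, or age-band term, is the rate for a child at the centre of the random-effect distribution. Because the exponential is convex, that rate is lower than the population average whenever children differ in their underlying risk.

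The mixed model is the only inferential method that the section names for incidence. An analyst who takes the rate and interval that it returns by default would therefore report an interval for a different quantity from the rate beside it. For febrile illness the gap could be large. For typhoid, very few children will have two confirmed episodes, so the data carry almost no information on the variance and the fit can depend on a single child.

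**Working it through.** **1. The plan's own figure.** 5600 children × 1.5 years = 8400 child-years = 2400 + 3000 + 3000. With 26 cases the rate is 26/8400 = 3.10 per 1000. Exact Poisson limits (chi-square form) are 2.02 to 4.54, which exclude 2 per 1000. With 25 cases the lower limit is 1.93. The threshold of 26 reproduces and is not in question here.

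**2. Conditional against population rate.** Let child i have rate exp(b0 + u), with u normal, mean 0 and variance s². The population rate is E[exp(b0 + u)] = exp(b0 + s²/2), so exp(b0) = population rate × exp(-s²/2). The documents give no s²; the values below are assumptions.

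| s² | exp(-s²/2) | a true 4.00 per 1000 becomes |
|---|---|---|
| 0.1 | 0.95 | 3.80 |
| 0.25 | 0.88 | 3.53 |
| 0.5 | 0.78 | 3.12 |
| 1 | 0.61 | 2.43 |
| 2 | 0.37 | 1.47 |

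The factor is the same in every age band under a common random intercept, so it cancels in age rate ratios.

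**3. Febrile illness.** Assume one episode per child-year (no rate is given in the article), and 5600 children followed for 1.5 years. Random-intercept Poisson fits to simulated data gave these medians, in episodes per child-year:

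| true s² | crude | exp(b0) | exp(b0 + s²/2) |
|---|---|---|---|
| 0.25 | 1.00 | 0.88 | 1.00 |
| 0.5 | 1.00 | 0.78 | 1.00 |
| 1 | 1.00 | 0.61 | 1.00 |

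The variance is well estimated because about 1870 to 2300 children have two or more episodes. Averaging over the random effect recovers the crude rate. In a separate data set with a mean-1 gamma random effect, the crude rate and the exponentiated intercept were both 0.982.

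**4. Typhoid, usual case.** At 3.10 per 1000, the expected number of children per site with two or more episodes is 0.06 at s² = 0 and 0.39 at s² = 2. In simulations with true s² of 0, 0.5 and 1, the fitted variance was essentially zero in 96%, 90% and 85% of runs, and exp(b0) then equals the crude rate.

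**5. Typhoid, one repeat.** These are constructed data with 5600 children, 1.5 years each and rates per 1000. The mixed model was fitted by maximum likelihood with Gauss-Hermite quadrature and Wald limits on the log scale.

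| data | crude (exact 95% CI) | fitted s² | exp(b0) (95% CI) |
|---|---|---|---|
| 26 cases, no repeat | 3.10 (2.02 to 4.54) | 0 | 3.10 |
| 26 cases, one child twice | 3.10 (2.02 to 4.54) | 3.1 | 0.65 (0.13 to 3.37) |
| 33 cases, no repeat | 3.93 | 0 | 3.93 |
| 34 cases, one of those 33 children twice | 4.05 | 2.4 | 1.22 (0.30 to 4.89) |

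In the second row the exact interval excludes 2 per 1000 and the conditional interval does not. The marginalised rate, exp(b0 + s²/2), is still 3.10. Poisson regression with child-clustered robust variance on the same data gives 3.10 (2.08 to 4.61), which also excludes 2 per 1000. Between the last two rows, one extra case lowers the conditional rate by 1 - 1.22/3.93 = 69%.

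**The case against.** The strongest reply is that the plan has already fixed the right estimand. It defines the rates twice as events over person-time and brings in the mixed model only to deal with correlation. Nothing says that the intercept will be the reported incidence. That is right, and the point estimates are not at fault.

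A reader might go further and infer that the reported rates will be biased downward. The documents do not support that. It needs a normal random effect, reporting of the conditional rate, and no averaging over the random effect. The first is the ordinary meaning of the named model, but the article states none of the three. A mean-1 gamma random effect, or marginal predictions, would remove the shift.

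It is also fair to say that the typhoid fit usually collapses to zero variance, where there is no shift, and that age comparisons are not distorted. The variances and the febrile illness rate used above are assumptions.

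Finally, the random-effect distribution and the type of prediction can be left to an analysis plan, and their absence is no fault. What remains is the stated choice itself: the one method named does not by default give an interval for the rate defined in the same section.

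**Conclusion.** The point holds as a mismatch between the defined rate and the named method. It is not a finding that the incidence estimates are wrong.

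- **Acute febrile illness:** if the model's default rate and interval were reported, they would be about 12%, 22% or 39% below the population rate at assumed variances of 0.25, 0.5 or 1.
- **Typhoid:** the risk is occasional instability, not routine bias. With the planned 26-case threshold, one repeat case is enough to move the model rate from 3.10 to 0.65 per 1000 and to lose the exclusion of 2 per 1000.
- **Unaffected:** the crude point rates, age rate ratios and the sample-size threshold.

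The sizes rest on a normal random intercept, no averaging over it, 5600 children followed for exactly 1.5 years, and the assumed variances and febrile illness rate. The change is worth making before analysis.

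**What to change.** In the Data analysis section, keep the crude rates as defined and say how their intervals are obtained:

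- Fit a marginal model by age band: Poisson regression with log person-time as offset and robust variance clustered on the child, or GEE. With age band as the only factor and the Poisson model, this returns the crude rates exactly.
- Use exact Poisson limits for typhoid where counts are small; repeats are then too rare for correlation to matter much.
- If the mixed model is kept for covariate effects, report from it only rates averaged over the random effect.

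This is one or two sentences of analysis text. It needs no new data and no change to the design or sample size, and the methods are available in the software already named.
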